#### Implementation

Our biostatistician generated a computerised randomisation allocation code. The research assistant will assign study participants to one of the three interventions in this study based on the generated allocation code.

#### Blinding

Participants and the medical team responsible for their treatment and care will be blind to the assignment of the intervention a participant receives. As this study does not interrupt, change or affect clinical care, the unblinding of participants will not be permissible.

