### Objectives and hypothesis

Our proposed research seeks to mitigate the problems of poor recall by piloting three different strategies concurrently and to assess the feasibility of these strategies in a busy hospital clinical environment. The first strategy is to evaluate the use of tablet computer technology’s audio-visual functionality as a way to improve the validity of recall of health status among trial participants with COPD. The method involves making an audio-visual recording of the participant’s initial responses to a quality of life questionnaire. Participants will be able to see their image and reflect on how they look at the baseline, and listen to how they sound prior to completing the follow-up questionnaires. This audio-visual recording will act as frame of reference and as an anchor to their past health status to aid their memory. The second strategy is the provision of access to the patient’s previous completed baseline questionnaire prior to completing their follow-up questionnaire. The third strategy is current practice of completing quality of life questionnaires independent of previous responses.

Specifically, we are seeking to understand among patients with COPD undergoing pulmonary rehabilitation, what is the change that occurs in patient-reported measurement when tablet computer technology is used to audio-visually record patients’ responses to health questionnaires on their subsequent ability to recall their previous health status? Secondly, we are assessing whether the provision of previous responses to quality of life questionnaires differs between COPD patients who are enrolled in pulmonary rehabilitation and those who are waiting to commence the program. Thirdly, we will compare the current practice of completing quality of life questionnaires before and after the program. Finally, we will be assessing the feasibility of conducting this study in a busy acute care clinical environment. Our hypothesis is that the magnitude of the difference (responsiveness) between groups of COPD patients will be greatest in those who saw the audio-visual recording.

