#### Interventions

Study participants will be randomly allocated to one of the following strategies to enhance patient recall (Fig.1):Tablet computer technology audio-visual recording: As part of recording participants at baseline, they will be asked to respond to questions on the health questionnaires which they have just completed by self-report. Participants will be shown this video 1 month later prior to the completion of the follow-up questionnaires.Shown hard copy of baseline responses: Participants will be provided with hard copies of their baseline responses to review immediately prior to completing follow-up questionnaires.Standard practice: Participants will be required to complete the health questionnaires at baseline and 1 month later without access to their previous responses or an audio-visual recording and receive no feedback on their baseline responses.

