### Data collection, management and analysis

#### Data collection methods

Consenting, enrolled participants will be assessed at baseline and again 1 month later at the follow-up appointment. The research assistant will record the patient’s demographic information, clinical history, comorbid conditions, medical therapy and past activity and exercise history. The participant will complete the following patient-reported outcome questionnaires at baseline and again 1 month later.European Quality of Life tool that has five dimensions and questions (EQ5D) [19]The Health Survey Short Form with 36 questions (SF36) [20]St Georges Respiratory Questionnaire (SGRQ) [21]Hospital Anxiety and Depression Scale (HADS) [22]

Functional measurements will also be completed at baseline and 1 month later. These include six-minute walk test and lung function testing comprising forced expired volume over 1 s.

Feasibility of conducting this study will be assessed over the course of the study and the following data recorded (Table 1).Willingness of clinicians to refer patients to the studyWillingness of participants to be involved in the studyNumber of eligible patientsCount of participant’s who drop-outFollow-up ratesLength of time to complete recruitment (months)Length of time (min) needed to administration the questionnairesLength of time (weeks) required to complete data analysis

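### The protocol says participants are blind to their intervention, but two of the three arms see it just before they rate themselves at follow-up

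*Protocol article*

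**What the plan says.** The Blinding section makes an unqualified statement: "Participants and the medical team responsible for their treatment and care will be blind to the assignment of the intervention a participant receives". It adds that "the unblinding of participants will not be permissible".

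The Interventions section describes three arms that differ openly. In the tablet arm, participants are filmed at baseline, and "Participants will be shown this video 1 month later prior to the completion of the follow-up questionnaires". In the second arm, "Participants will be provided with hard copies of their baseline responses to review immediately prior to completing follow-up questionnaires". The standard-practice arm completes the questionnaires "without access to their previous responses or an audio-visual recording and receive no feedback on their baseline responses". For the film, Objectives and hypothesis gives the purpose of the viewing: "Participants will be able to see their image and reflect on how they look at the baseline".

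The outcome instruments are the EQ5D, SF36, SGRQ and HADS. Data collection methods says: "The participant will complete the following patient-reported outcome questionnaires at baseline and again 1 month later". Statistical methods compares the strategies on the difference in mean change between rehabilitation and wait-list participants, and predicts the largest difference in the audio-visual arm.

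On who knows the allocation, Implementation says: "The research assistant will assign study participants to one of the three interventions in this study based on the generated allocation code". Allocation concealment mechanism adds that this assistant keeps the code, and that investigators and clinical staff do not know the assignment. Under Eligibility criteria, the same assistant interviews participants at baseline and one month later.

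**The concern.** A person who has just watched a film of themselves, or has just been handed their own earlier answers, knows which of these they received. The Blinding section says they do not.

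This matters because the participant is the one who rates the outcome. Someone who has begun rehabilitation and is then shown how they looked and sounded beforehand may report improvement because it seems to be expected. If so, responsiveness would rise in the arm that the hypothesis favours, for a reason other than better recall. A statement that participants are blind invites the reader to set that explanation aside. The Sample size section says the pilot data will supply parameters for a larger trial of the audio-visual recording, so the misdescription could be carried into that design.

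**Working it through.** The plan gives no figure for this point, so there is none to reproduce. The check sets the sections side by side, makes one count, and asks what the planned comparison can identify.

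**Step 1: what the participant can see (Interventions).**

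| Arm | When baseline forms are completed | Just before follow-up forms |
|---|---|---|
| Audio-visual | Not yet filmed; filming follows the forms | Watches own film |
| Hard copy | Nothing specific to the arm | Reads own baseline answers |
| Standard practice | Nothing specific to the arm | Neither |

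Nothing described in the procedures reveals the arm while the baseline forms are being completed. At follow-up, the first two arms cannot be unaware of what they received. In the standard arm, no described measure keeps participants unaware that they received neither.

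**Step 2: how many ratings.** Inputs are 30 participants (Sample size) and a 1:1:1 ratio (Sequence generation).

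- Follow-up ratings from participants who have just seen their material: 30 × 2/3 = 20 of 30.
- Rating occasions over both time points: 30 × 2 = 60. The affected share is 20/60, or one third.

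Both counts assume an exact split and complete follow-up. Randomisation is 1:1:1 within the rehabilitation and wait-list groups separately. Their sizes are in Fig. 1, which is not shown, so 20 is approximate.

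**Step 3: what the comparison identifies.** For any one strategy, write responsiveness as

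R = (mean change in rehabilitation) − (mean change on the wait list).

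Let r be the shift in reported change that comes from better recall, and d the shift that comes from demand or expectation. Relative to having no strategy, R moves by

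(r_rehab − r_wait) + (d_rehab − d_wait).

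The trial estimates only this sum. If demand acts equally in both groups, the second term is zero and it cancels. If it acts more strongly in rehabilitation participants, who know they are being treated, it enlarges R. No arm receives the film without knowing it, so the two terms cannot be separated. Comparing the audio-visual arm with the hard-copy arm would remove only the demand that any reminder of baseline creates, not demand specific to the film. The documents give no basis for a value of d.

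**The case against.** The best defence is that the authors meant something narrower: that participants are not told the hypothesis, or that the hard-copy and standard arms look alike until follow-up. Either may be true, but the section says neither. It says participants are blind to the intervention they receive. Under the second reading, the masking has gone by the time the follow-up questionnaires are rated.

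Several limits stand.

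- A reader might infer that two thirds of all outcome assessments are affected. Baseline forms come before any material is shown, so the share is two thirds at follow-up and one third overall.
- A reader might infer that the protocol claims blinding protects the self-reported outcome. It never says so; that is only the usual purpose of such a statement.
- A reader might infer a false claim about the research assistant. There is none. The assistant's role is stated openly, the Blinding section does not list the assistant as blind, and eligible patients must read well enough to complete the questionnaires without help. The Blinding section should simply state the assistant's position.
- Seeing one's earlier self is largely the intended mechanism, so an audio-visual effect cannot be written off as bias. Only pressure to report improvement counts as bias, and it must differ between rehabilitation and wait-list participants to affect R.
- What participants are told about the arms or the hypothesis is in consent material that is not shown. No fault can be found with it here.

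**Conclusion.** The blinding statement is wrong as written for participants in the audio-visual and hard-copy arms at follow-up: about 20 of 30, assuming the planned ratio is met and all return. No other section restores it. Blinding of the medical team and investigators is plausible and is not disputed.

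The consequence is limited to the secondary responsiveness comparison and to the estimates taken from it for a larger trial. The feasibility counts and times do not depend on participant blinding. The size of any demand effect is unknown, and its direction is a possibility rather than a finding. The documents do not support the stronger conclusion that the responsiveness result will be biased, or that the design must change. They support the narrower one that a stated property of the design is absent, and that a favourable audio-visual result would have more than one explanation.

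**What to change.** 1. Replace the participant-blinding statement, and the ban on unblinding participants that depends on it. Say instead that participants are not blinded to the strategy they receive; that the research assistant, who keeps the code, assigns arms and conducts the interviews, is not blinded; and that the clinical team and investigators are.
2. Keep the arms under neutral codes in the dataset until the analysis is locked. Access to data gives all investigators the final dataset, and coding lets the investigator masking stated under Allocation concealment mechanism hold through the analysis. The protocol makes no claim about masking during analysis, so this is an addition rather than a correction.
3. Add to Statistical methods or the Discussion that greater responsiveness in the audio-visual arm cannot be separated from demand or expectation effects on self-report, and that estimates carried to the larger trial share this limit.

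The cost is a few sentences of protocol text and one recoded variable. Allocation, interventions, visits and sample size are unchanged.

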### Data collection, management and analysis

#### Data collection methods

Consenting, enrolled participants will be assessed at baseline and again 1 month later at the follow-up appointment. The research assistant will record the patient’s demographic information, clinical history, comorbid conditions, medical therapy and past activity and exercise history. The participant will complete the following patient-reported outcome questionnaires at baseline and again 1 month later.European Quality of Life tool that has five dimensions and questions (EQ5D) [19]The Health Survey Short Form with 36 questions (SF36) [20]St Georges Respiratory Questionnaire (SGRQ) [21]Hospital Anxiety and Depression Scale (HADS) [22]

Functional measurements will also be completed at baseline and 1 month later. These include six-minute walk test and lung function testing comprising forced expired volume over 1 s.

Feasibility of conducting this study will be assessed over the course of the study and the following data recorded (Table 1).Willingness of clinicians to refer patients to the studyWillingness of participants to be involved in the studyNumber of eligible patientsCount of participant’s who drop-outFollow-up ratesLength of time to complete recruitment (months)Length of time (min) needed to administration the questionnairesLength of time (weeks) required to complete data analysis

#### Data management

All data will be stored on a password-protected computer in a university research office with security swipe access. Participant data will be entered into SPSS version 23 study database from hardcopy completed questionnaires and study forms that record the functional assessments. Data will be audited after the first 15 participants’ data have been enrolled and their data entered onto the database and at the end of the study prior to data analysis to ensure data quality and accuracy. The audit will be a comparison between the hard copy of the completed questionnaires and the entered data.

#### Statistical methods

Demographic and clinical information will be assessed using descriptive statistics measuring frequencies, means and standard deviations. We will measure the within-subject change in PRO questionnaire scores over the 1-month period. The difference in mean change between those who had pulmonary rehabilitation and those who remained on the waiting list over this 1-month period will be calculated. Finally, the magnitude of this difference (responsiveness) of these scores will be compared between groups. Our hypothesis is that the magnitude of the difference (responsiveness) will be greatest in those who saw the audio-visual recording.

Feasibility will be reported using descriptive statistics such as frequencies, rate, means and standard deviations to interpret whether it is feasible to conduct a larger study in this busy clinical environment.

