## Methods

This is a pilot randomised control parallel group trial of three strategies to improve patient recall in the self-report of health status using quality of life questionnaires. These strategies to aid patient recall will be tested in a single centre, randomised controlled trial comparing alternative strategies of assessing change in patient reported outcomes with treatment in an acute care hospital in Australia. The parallel groups comprise COPD patients commencing pulmonary rehabilitation and COPD patients waiting to commence the program. We will compare three strategies to improve patient recall with the standard approach of patient’s completing the questionnaires at each study time point. These new strategies in addition to current practice are (1) the use of tablet technology’s audio-visual functionality and (2) the provision of patient access to their baseline questionnaire responses prior to completion of questionnaires at follow-up. Additionally, we are assessing the feasibility of using these patient strategies to improve patient recall when completing self-report PROs questionnaires in a busy acute care hospital. Feasibility will be assessed according to the National Institute for Health Research (NIHR) feasibility study criteria (Table 1) [18].

**Table 1 Tab1:** Feasibility assessment for recall study

Feasibility item	Record
Willingness of clinicians to refer patients to the study	Number of referrals to study
Willingness of participants to be involved in the study	Number of patients approached but chose not to participate
Number of eligible patients	Number of patient who are eligible based on criteria
Number of participants that dropped out of study	Number of participants who withdrew and reasons or died
Follow-up rates	Number of participants who completed time 2 questionnaires
Length of time to complete recruitment of participants	Time in months
Length of time to administer intervention	Time in minutes
Length of time to analyse data	Time in days

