**Fig. 1 Fig1:**
[figure not shown]
Study participant numbers in each group and study interventions protocol

Clinical care will not be affected and the clinical team will continue the medical management of the patient during the timeframe of the study. The investigator team members are not part of the clinical or pulmonary rehabilitation teams. Patients who become clinically unwell and unable to attend the follow-up appointment will be included in the analysis.

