#### Outcomes

There are two outcomes associated with this study; evaluating the feasibility of conducting this study in an acute tertiary admission hospital using the National Institutes for Health Research’s feasibility criteria and testing the hypothesis related to the difference in quality of life indices. The feasibility outcome for this study is the ability to recruit participants who are wait-listed or attending the pulmonary rehabilitation program, administer the interventions in a timely manner and the ease of conducting and completing this study in a busy clinical environment without disruption to the pulmonary rehabilitation service or patient care. The secondary outcome of this randomised controlled trial is concerned with the impact of the patient recall strategies on the quality of life questionnaires’ responsiveness. Specifically, we are measuring the magnitude of statistical difference of quality of life between the three arms of the study.

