#### Sample size

For this pilot randomised control trial and feasibility study, we did not generate a sample size. Thirty (30) adults with COPD, who are either commencing or wait-listed for pulmonary rehabilitation, will be enrolled in this study. The data generated from this study will be used to estimate important parameters that are required to design a larger randomised controlled study to evaluate the role audio-visual recordings using tablet computer technology may play in assisting patient’s recall of their previous health state.

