#### Sequence generation

Eligible participants will be randomised 1:1:1 assigned ratio to one of the three intervention arms in both the pulmonary rehabilitation and wait list groups using the computer-generated randomisation code.

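### Outcomes and Statistical methods set two different comparisons for the same secondary hypothesis; only the recall strategy by rehabilitation/wait-list contrast measures responsiveness, and it should be estimated, not ranked

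*Protocol article*

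**What the plan says.** All references are to the protocol article.

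- **Outcomes.** The secondary outcome is the effect of the recall strategies on the responsiveness of the questionnaires. The next sentence makes this concrete: "Specifically, we are measuring the magnitude of statistical difference of quality of life between the three arms of the study".
- **Statistical methods.** Within-subject change over one month is computed, then the difference in mean change between rehabilitation and wait-list patients. The last step is: "Finally, the magnitude of this difference (responsiveness) of these scores will be compared between groups". The analysis is described on change scores, without baseline adjustment.
- **Hypothesis** (Objectives and hypothesis; repeated in Statistical methods). The difference is expected to be largest among patients shown the video. The article attaches no test, interval or threshold to this.
- **Methods, opening paragraph.** On the trial's structure: "The parallel groups comprise COPD patients commencing pulmonary rehabilitation and COPD patients waiting to commence the program".
- **Sequence generation.** On how strategy is allocated: "Eligible participants will be randomised 1:1:1 assigned ratio to one of the three intervention arms in both the pulmonary rehabilitation and wait list groups".
- **Sample size.** On the number: "Thirty (30) adults with COPD, who are either commencing or wait-listed for pulmonary rehabilitation, will be enrolled in this study"; on its basis, "we did not generate a sample size"; on its use, "The data generated from this study will be used to estimate important parameters that are required to design a larger randomised controlled study".
- **Fig. 1.** The caption reads "Study participant numbers in each group and study interventions protocol", but the figure is not in the text reviewed, so the rehabilitation/wait-list split is not known here.

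**The concern.** The Outcomes sentence compares three arms. The Statistical methods sentences compare a difference of differences. The first asks whether a recall strategy changes the scores patients report. The second asks whether it changes how well the questionnaire separates treated from untreated patients. The article's introduction ties responsiveness to detecting change, so only the second answers the trial's question.

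The word *groups* adds to the problem. In the Methods section, and most naturally in the hypothesis under Objectives, it means rehabilitation and wait-list. In the last step of Statistical methods it has to mean the recall arms, because the difference between rehabilitation and wait-list has just been taken.

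Two things are at stake. The conclusion about the video could rest on either contrast, and the two can disagree completely. The pilot is also meant to supply design parameters for a larger trial, and the two contrasts have very different precision for the same number of patients. Wording the hypothesis as a ranking also invites a claim from the order of three noisy estimates.

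**Working it through.** The plan states no power, alpha, effect size or SD, so it has no figure to reproduce. All results are in units of s, the SD of an individual's one-month change.

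**1. The two comparisons differ.** Let R_a and W_a be the mean change in rehabilitation and wait-list patients in recall arm a.
- Comparison A (Outcomes, applied to change with equal cells): (R_a + W_a)/2, compared between arms.
- Comparison B (Statistical methods): D_a = R_a − W_a, compared between arms.

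Suppose the video adds c to every follow-up answer. Then A for video versus standard is c, and B is (R + c) − (W + c) − (R − W) = 0. Suppose instead that the video raises R by d/2 and lowers W by d/2. Then A is 0 and B is d. Each comparison can be empty where the other is not.

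**2. Cell size.** There are 30 patients (Sample size), 3 arms and 2 groups (Sequence generation). Assuming an even 15:15 split, 30/6 = 5 per cell.

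**3. Precision of B, video versus one other arm.**
- SE = s·√(4/5) = 0.894s.
- Degrees of freedom 6 × (5 − 1) = 24, t = 2.064. The 95% half-width is 2.064 × 0.894s = 1.85s.
- At 7:3 within each arm of 10: SE = s·√[2(1/7 + 1/3)] = 0.976s, half-width 2.01s.
- At 8:2: SE = s·√[2(1/8 + 1/2)] = 1.118s, half-width 2.31s.

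**4. Precision of A on change scores.** With 10 per arm, SE = s·√(2/10) = 0.447s. With 27 df (t = 2.052) the half-width is 0.92s. The variance ratio of B to A is 0.8/0.2 = 4. For a numerically equal target difference and the same SD, a trial sized on A would have a quarter of the patients that B needs.

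**5. Ranking.** With three equal arms and no arm effect, symmetry gives the video arm a 1/3 chance of the largest D_a. Simulation (1,000,000 trials per setting) gives 0.332 to 0.333 at 3, 5, 10, 50 and 500 per cell, and 0.333 at the 7:3 and 8:2 splits. Sample size does not enter. It matters once there is a true effect: with a true video advantage of 0.5s, the video arm ranks first 57% of the time at 5 per cell and 93% at 50 per cell.

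**6. Baseline adjustment.** Take equal SD σ at both visits and correlation ρ between them.
- Change score variance: 2σ²(1 − ρ).
- Baseline-adjusted residual variance: σ²(1 − ρ²).
- Ratio: (1 + ρ)/2, which is 0.75 at ρ = 0.5 and 0.90 at ρ = 0.8 (ρ is assumed; the article gives none).
- With one degree of freedom spent (23 df, t = 2.069), the half-width of B is 2.069 × 0.894s × √0.75 = 1.60s to 2.069 × 0.894s × √0.90 = 1.76s. This ignores the small extra variance from chance baseline imbalance.

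**The case against.** The best defence is that the Outcomes sentence is loose shorthand. The sentence before it names responsiveness, and the hypothesis is framed as responsiveness in both places where it appears. That is plausible as to intent and lowers the severity. It does not remove the conflict, because the sentence meant to be specific names the wrong contrast. An unseen analysis plan could not settle which of two stated comparisons the protocol means.

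It is also fair to say that this is a secondary outcome in a 30-patient pilot that claims no sample size calculation. Low power for an interaction is expected there and is not an error. Details such as a lead questionnaire can properly sit in an analysis plan, so their absence is not part of this point.

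Some stronger readings that a reader might infer do not stand:
- **Small cells cause the one-in-three chance.** They do not; it holds at any cell size. Small cells cause the wide interval.
- **The hypothesis is decided by ranking first on any one of the four questionnaires.** The article sets no such rule. Being the greatest is how the hypothesis is worded, and Outcomes speaks of testing it.
- **Unadjusted change biases the arm contrast through selection into rehabilitation or wait-list.** Strategy is randomised within both groups, so that selection cancels in expectation between arms. It affects only each arm's own rehabilitation-minus-wait-list difference.
- **The observed effect will size the next trial.** The article says only that parameters will be estimated.

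**Conclusion.** The point holds at moderate severity. Two sections state different comparisons for one secondary hypothesis, and the word that should identify the comparison is used in two senses. Only the strategy by rehabilitation/wait-list contrast, taken across recall arms, matches the trial's question. The article describes it on unadjusted change and words the expected result as a ranking.

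As to size: a first rank for the video arm carries a 1/3 chance under no effect. This rests on equal arms, which the 1:1:1 allocation intends. The contrast itself would have a 95% half-width of about 1.85 SD. That rests on an assumed 5 per cell, full follow-up and a common SD, and it widens to 2.01 or 2.31 SD at 7:3 or 8:2. Baseline adjustment narrows it only modestly, so the main gain from the change is a single, correctly defined quantity reported with its uncertainty.

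**What to change.** 1. Align Methods, Outcomes and Statistical methods on one estimand: the strategy by (rehabilitation versus wait-list) contrast in the one-month score. Replace the three-arm sentence in Outcomes accordingly.
2. In the last step of Statistical methods, write recall arms in place of *groups*. In Methods, describe rehabilitation/wait-list as a non-randomised stratum within which strategy is randomised.
3. For each questionnaire score, fit the one-month score on baseline score, group, strategy and group × strategy. Report the video-versus-standard and video-versus-hard-copy interaction contrasts with 95% confidence intervals.
4. State that these are estimates and that the order of the arms alone supports no claim.

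The cost is wording and one degree of freedom per model. Baseline and one-month scores are already planned under Data collection methods, so no new data are needed. The downside is a less assertive conclusion about the video.
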